## Abstract

**Background:**

Currently, there are no disease-modifying pharmacological treatment options for dementia with Lewy bodies (DLB). The hallmark of DLB is pathological alpha-synuclein (aS) deposition. There are growing amounts of data suggesting that reduced aS clearance is caused by failure in endolysosomal and authophagic pathways, as well as and glucocerebrosidase (GCase) dysfunction and mutations in the GCase gene (GBA). The population’s studies demonstrated that the incidence of GBA mutations is higher among Parkinson’s disease (PD) patients, and carriers of such mutations have a higher risk of developing PD. The incidence of GBA mutations is even higher in DLB and a genome-wide association study (GWAS) confirmed the correlation between GBA mutations and DLB. *In vivo* experiments have shown that ambroxol (ABX) may increase GCase activity and GCase levels and therefore enhance aS autophagy-lysosome degradation pathways. Moreover, there is an emerging hypothesis that ABX may have an effect as a DLB modifying drug. The aims of the study “Ambroxol in new and early Dementia with Lewy Bodies (ANeED) are to investigate the tolerability, safety and effects of ABX in patients with DLB.

**Methods:**

This is a multicentre, phase IIa, double-blinded, randomised and placebo-controlled clinical trial, using a parallel arm design for 18 months’ follow-up. The allocation ratio is 1:1 (treatment:placebo).

**Discussion:**

The ANeED study is an ongoing clinical drug trial with ABX. The unique, but not fully understood mechanism of ABX on the enhancement of lysosomal aS clearance may be promising as a possible modifying treatment in DLB.

**Trial Registration:**

The clinical trial is registered in the international trials register – clinicaltrials.com (NCT0458825) and nationally at the Current Research Information System in Norway (CRISTIN 2235504).

## Background

In our memory clinics in Western Norway, approximately one in five patients is recognized to have dementia receive the diagnosis of dementia with Lewy bodies (DLB) – a disease associated with a more rapid decline, earlier nursing home admission and death, higher caregiver burden and higher levels of behavioural and psychiatric symptoms (BPSD) than in Alzheimer’s disease (AD) (Rongve et al., 2013). After Robin Williams’ suicide due to severe DLB, awareness of the disease rose, increasing disease recognition and priority. The DLB Association established research priorities with a focus on creating infrastructure for clinical trials and more resources to develop new therapeutics in 2019 (Peterson et al., 2019). Currently, there is no disease-modifying treatment for DLB (Lee et al., 2019).

Among the challenges associated with clinical trials in DLB are lack of standardised clinical assessment tools, lack of established and standardised biological markers, heterogeneity of DLB symptomatology and disease course and, importantly, difficulties regarding early identification of the disease (Goldman et al., 2020).

Lessons learned from many unsuccessful clinical trials on symptomatic AD have led to the conclusion that disease modifying treatment should be initiated as soon as possible, ideally in the pre-clinical stages (Cummings et al., 2018). Early interventions are required before extensive, evident neuronal damage such that the effectivity of pharmacological treatment reaches its full potential, and patients in prodromal stages must therefore be included in clinical trials. Over time, the recognition of the prodromal stages of DLB has increased, including subjective cognitive (SCD) and mild cognitive impairment (MCI). For the first time, diagnostic research criteria were recently published (McKeith et al., 2017). As clinical symptoms are even less specific and less pronounced in the prodromal stage, sensitive and specific biomarkers are crucial for timely and accurate diagnosis of prodromal DLB and for prediction of conversion towards DLB. Because of the unfulfilled promises of newly developed drugs for AD and the sustained lack of a new pharmacological strategy in DLB, researchers have focused on drug repurposing or repositioning in neurodegenerative disorders.

The hypothesis that ambroxol (ABX) could potentially be useful in DLB originated in studies on Gaucher disease (GD), a lysosomal storage disorder, caused by a mutation in the glucocerebrosidase (GCase) gene (*GBA1*) and resulting in the development of parkinsonism in some patients (Tayebi et al., 2003). This has led researchers to discover that mutations in *GBA1* are a genetic risk factor for synucleinopathies similar to Parkinson’s disease (PD) and DLB (Goker-Alpan et al., 2004; Lwin et al., 2004). Between 2 to 30% of patients with PD have *GBA1* mutations, increasing the risk of PD up to 20–30 fold (Neumann et al., 2009). The frequency is even higher in DLB, particularly in Ashkenazi Jews (Donaghy et al., 2018). One of the studies demonstrated a significant association between *GBA1* mutation carrier status and other synucleinopathies such as DLB. Subjects with DLB were more than 8 times more likely to carry a *GBA1* mutation than controls (Nalls et al., 2013). The mechanisms by which *GBA1* mutations resulted in Parkisonian symptoms in GD have been unclear until researchers found a link between GCase activity and alpha-synuclein (aS). GCase deficiency causes pathologic accumulation of aS (Velayati et al., 2010; Cullen et al., 2011), while GCase overexpression in the brain or gene therapy may reduce pathology and memory deficits in a synucleinopathy mouse model (Sardi et al., 2011). PD and DLB patients without GCase mutation also exhibit lower levels of GCase activity in the central nervous system (CNS), and this is related to earlier disease onset and worse cognitive and non-motor symptoms (Gegg et al., 2012; Chiasserini et al., 2015). This suggests a potential contribution of the GCase activity in disease pathogenesis, possibly by alteration of lysosomal function. Modulation of the enzyme’s activity might increase the lysosomal autophagic clearance of aS (Papadopoulos et al., 2018).

Unfortunately, current treatment for patients with GCase deficiency by enzyme replacement or gene therapy is not sufficient or successful in all patients. This is why researchers have begun to search for alternative treatment avenues. Some of them target the proteasome and autophagy dysfunction and include chaperone-mediated autophagy (CMA) and macroautophagy (Webb et al., 2003; Vogiatzi et al., 2008; Wildburger et al., 2020). Such drugs were designed to bind and modify aS misfolding and promote lysosomal transport by improving GCase activity (Elkouzi et al., 2013; Bonam et al., 2021).

Nowadays, there is extensive research on the use of pharmacological chaperones to enhance lysosomal GCase activity, such as ABX, isofagomine or NCGC607 (Han et al., 2020).

ABX, a drug used to treat airway mucus hypersecretion, has shown effects in both animal models and human GD type 3 (GD3) with predominant neurological symptoms and PD (McNeill et al., 2014; Richards et al., 2016). Preclinical trials of ABX in models of synucleinopathies are promising, incising the effects of GCase and reducing the concentration of toxic aS species. For an overview of pre-clinical animal studies, see the supplementary materials. Here, we describe human studies.

The pilot study of five patients with GD3 and a positive *in vitro* chaperone test showed that high-dose ABX treatment had good safety and tolerability, significantly increased lymphocyte GCase activity, permeated the blood–brain barrier and decreased glucosylsphingosine levels in the cerebrospinal fluid, with motor improvement in two of them (Narita et al., 2016). Additionally, an over four-year-long study on the safety and efficacy of combined high-dose ABX (up to 27 mg/kg/day) and enzyme replacement therapy in four patients with GD3 and myoclonic epilepsy showed that seizure frequency significantly decreased from baseline, neurocognitive function improved and the drug was tolerated without severe adverse events (AEs) (Kim et al., 2020).

The first study on PD was a non-randomised, non-controlled trial phase IIa trial of 17 participants with mutation in *GBA1* and without. The results showed that ABX penetrated to the CNS, had a modulatory effect on GCase in cerebrospinal fluid (CSF) and increased total aS concentration in CSF. The researchers observed a tendency towards mild improvement in the total score of the motor part of Unified Parkinson1s disease Rating Scale (UPDRS), but the lack of a placebo group made it difficult to interpret the findings. The treatment was safe and well tolerated (Mullin et al., 2020). The second study on Parkinson’s disease dementia (PDD) randomised, placebo controlled and quadruple masked with 75 participants started in 2015 (Silveira et al., 2019). The study completed inclusions and follow-ups, and preliminary results showed that ABX has been well tolerated and that there were no severe AEs judged to be due to ABX. The researchers also reported that GCase levels in white blood cells increased by 1.6-fold (oral report on the AD/PD conference, Barcelona 2022).

There are other ongoing or planned studies on ABX in DLB. One of them is a placebo-controlled study of 15 participants with DLB, which will last 52 weeks ([name], Lawson Health Research Institute, London, Ontario, Canada). The estimated study completion is September 2024 (NCT04405596). The same centre is responsible for the study “Ambroxol as a Treatment for Parkinson’s Disease Dementia” in 75 individuals with PDD. The researchers estimated study completion to December 2021 (NCT02914366), but the results are as of yet not published. The researchers from Israel started the register for patients with GD and GBA carriers with PD (300 participants). The goal of this register is to complete data within 10 years and further use this as a reference for patients, caregivers and physicians who consider the use of ABX (REGISTRY for the Collection of Real World Data on the Safety and Efficacy of Ambroxol – World Data on Ambroxol for Patients with GD and GBA Related PD; [name], Shaare Zedek Medical Centre [NCT04388969]). For a better overview of clinical trials with ABX, see Table 1.

**Table 1 tab1:** Clinical studies on ambroxol in synucleinopathies.

Study/type	Dgn.	Status	Dosing	N	Duration	Main outcome
Ambroxol as a Treatment for Parkinson’s Disease Dementia, London, Canada	PDD	Ongoing, NCT02914366	1,050 mg oral	55	52 weeks	ADAS-cog
Ambroxol in Disease Modification in Parkinson Disease (AIM-PD), London, United Kingdom	PD	Completed	1,260 mg oral	20	6 months	Safety, tolerability and pharmacodynamics
Ambroxol as a Novel Disease Modifying Treatment for Lewy Body Dementia, London, Canada	DLB	Not yet recruiting, NCT04405596	1,350 mg oral	15	52 weeks	MMSE
Ambroxol as a disease-modifying treatment in GBA-PD (AMBITIOUS), multicenter, Italy	PD	Ongoing, NCT05287503	1,200 mg oral	60	52 weeks	MoCA
Ambroxol in New and Early DLB, A Phase IIa Multicenter Randomized Controlled Double Blind Clinical Trial (The ANeED Study), multicenter, Norway	DLB	Ongoing, NCT04588285	1,260 mg	172	18 months +12 months open extension	MMSE

ADAS-cog, the Alzheimer’s Disease Assessment Scale-Cognitive Subscale; DLB, Dementia with Lewy bodies; MMSE, the Mini Mental State Examination; MoCA, the Montreal Cognitive Assessement; PD, Parkinson’s disease; PDD, Parkinson’s disease dementia.

The main objectives of our study are: 1) to assess the safety and tolerability of ABX at high dosage in DLB patients, 2) to examine the effect of ABX on the rate of cognitive decline and associated motor and non-motor DLB symptoms, 3) to study the effect of ABX on dementia markers in CSF, neuroimaging and neurophysiological markers (resting state EEG [rsEEG]), and 4) to study the rate of functional decline. If the drug tolerance is good, we hope that this study will provide new insights that can lead towards a new standard treatment for DLB.

### Methods

The team at Helse Fonna, Haugesund Hospital, Department of Research and Innovation is the sponsor and we designed the study protocol based on the published AIM-PD protocol (Silveira et al., 2019). The funding agency is the public and government organisation, KLINBEFORSK, the national program for clinical treatment research in the specialist health services.

### Design

This is a multicentre, phase IIa, double blinded, randomised and placebo-controlled clinical trial, using a parallel arm design for 18 months’ follow up. The allocation ratio is 1:1 (treatment:placebo). The participants will undergo detailed clinical assessments at the screening visit, baseline visit (day 1) and at weeks 4, 8, 24, 36, and 52 of the treatment phase. We will perform four phone controls in the escalation phase and at week 5, 12, 16, 20, 28, 32, 40, 44, and 48. Between screening visit and baseline (max. 90 days), we will perform mandatory lumbar punctures, MRI, DaTSCAN, ECG, rsEEG, blood analysis, clinical and cognitive assessments.

Each participant will receive five intra-participant dose escalations at 60 mg three times a day (TID) (days 1–7), 120 mg TID (days 8–14), 315 mg twice a day (BID) (days 15–28), 315 mg TID (days 22–28) and 420 mg TID (days 29–550) with ABX or placebo for the duration of 18 months. After this period, we will offer the treatment with ABX in an open-label extension phase for 12 months for all participants who will continue.

The study is carried out in seven Norwegian centres: Helse Fonna, Haugesund Hospital as the study-coordinating center and Haraldsplass Deaconess Hospital (Bergen), Stavanger University Hospital, Akershus University Hospital (Oslo), Oslo University Hospital, St. Olav Hospital (Trondheim) and the University Hospital of North Norway (Tromsø) are allocated study sites. The inclusion period began in May 2021.

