### Participants

Participants must fulfil the following inclusion criteria: a) diagnosis of possible or probable DLB or MCI-DLB according to the established McKeith criteria from 2017 and 2020, respectively (McKeith et al., 2017; IG et al., 2020), b) are in age range between 50 and 85 years, c) have MMSE score > 15 at screening, d) are on stable doses of antiparkinsonian or dementia or psychiatric medications at least 1 month prior to the study initiation, e) participant or participant’s caregiver are able to give informed consent to actual and further assessments and procedures and f) have a responsible caregiver >18 years old who has contact with the participant at least three times a week.

The main exclusion criteria are a) any clinically significant or unstable psychiatric, medical or surgical condition, b) major cardiovascular or cerebral event that occurred within 6 months prior to the first visit, c) advanced malign disease or other terminal illness, d) relevant medication, alcohol or drug abuse, e) known sensibility to or contraindication for ABX, f) female participants who are pregnant or currently breastfeeding, and g) not able to proceed with the study regime (i.e., like traveling to study site or dysphagia, or unable to perform supplementary examination because of contraindications, claustrophobia, etc.). For other detailed inclusion and exclusion, criteria see Table 2.

**Table 2 tab2:** Inclusion and exclusion criteria in the ANeED study.

Inclusion criteria	1. Age ≥ 50 and ≤ 85 years of age, both gender
	2. Confirmed diagnosis of DLB including mild cognitive impairment in DLB (DLB-MCI).
	3. MMSE score >=15 at screening
	4. Able and willing to provide informed consent prior to any study related assessments and procedures
	5. Capable of complying with all study procedures
	6. Willing to provide blood samples for genetic analyses of APOE and GBA
	7. Willing and able to self-administer or administer by a caregiver oral ambroxol medication, from day 1 to study end (at 60 mg TID (day 1-7), 120 mg TID (day 8- 14), 315 mg BID (day 15-21), 315 mg TID (day 22-28) and 420 mg TID (day 29-550)).
	8. Contact with caregiver at least 3 times a week, to ensure sufficient information from the caregiver regarding participant’s status and possible change in condition
	9. Able to travel to the participating study site

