### Randomisation and blinding

We will perform randomisation using the electronic case report form (eCRF) system (Viedoc^1^). The participants will be randomly assigned into two arms: ABX 1260 mg/d (in three doses per day) and placebo – in an allocation ratio of 1:1. Before randomisation, the participants will be stratified due to risk factors (number of APOEε4 alleles (0, 1, 2) and beta-amyloid in CSF: normal and low). Therefore, we will use a restricted randomisation method with blocking and stratification. The number of strata is six. The block size is 4 (McKeith et al., 2017) with number and blocks 6 (Webb et al., 2003). The independent data manager will provide randomisation, and the drug manufacturer will get the list and deliver drug kits numbered based on the stratification.

The patients, patient’s caregivers, all study personnel, monitors and statisticians are blinded until the end of the study, with the exception of an emergency unblinding procedure. The ABX and placebo are produced in a tablet form and identical in appearance and taste to blinding purposes. Placebo tablets with microcrystalline cellulose as the main compound will include denatonium benzoate as a residual amount of bitter substance as ABX tablets have. Each participant will get the investigation medical product (IMP) in sequentially numbered identical containers according to the randomisation schedule. The responsible pharmaceutical company, Kragerø Tablettproduksjon AS, will send IMP shipments directly to each participating centre for dispensing and storage for the study.

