From this point forward, the first 18-months phase treatment regime begins, and it is divided into the titrations phase and the maintenance phase. Initially, each participant will receive five intra-participant IMP dose escalations at 60 mg TID (baseline – day 7), next 120 mg TID (days 8–14), 315 mg BID (days 15–28), 315 mg TID (days 22–28), and 420 mg TID, a total of 1,260 mg/d. To track the side effects tied to the study drug, all patients will receive a weekly phone call in the dose-escalation phase to monitor safety and tolerability. Changes in medication use (other than the study drug), any AEs or falls will also be assessed during these phone calls. In the case of side effects, the PI can decide to deviate from the drug admission protocol in order to adjust or delay dose escalation.

All participants will have eight scheduled on-site visits: an initial screening, a drug administration visit, 6 follow-up visits, and a total 16 phone calls spread out over 18 months. Figure 1 shows the flow chart of the ANeED study’s schedule.

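### The titration text assigns both 315 mg BID and 315 mg TID to days 22–28 and conflicts with Table 2 on when the BID step ends

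*Protocol article*

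**What the plan says.** The protocol article states the titration schedule three times.

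- **Design:** "315 mg twice a day (BID) (days 15–28), 315 mg TID (days 22–28"), followed by 420 mg TID on days 29–550.
- **Interventions and assessment procedures:** "315 mg BID (days 15–28), 315 mg TID (days 22–28), and 420 mg TID, a total of 1,260 mg/d". No days are printed for the last step here.
- **Participants, Table 2, inclusion criterion 7:** "315 mg BID (day 15-21), 315 mg TID (day 22-28) and 420 mg TID (day 29-550").

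The first two steps are the same in all three places: 60 mg TID in week 1 and 120 mg TID on days 8–14. Randomisation and blinding gives the target as "ABX 1260 mg/d (in three doses per day) and placebo". Interventions and assessment procedures also gives the investigator latitude when side effects occur: "the PI can decide to deviate from the drug admission protocol in order to adjust or delay dose escalation".

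**The concern.** The Design and Interventions sections are the two that describe how the drug is given. In both, the BID step runs to day 28 while the TID step starts on day 22, so the last week before the target dose carries two regimens. The only version without an overlap sits in an eligibility criterion, and no order of precedence is given.

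What is at stake is the reference dose for that week. Safety and tolerability is the first main objective, and the first secondary outcome counts participants whose dose is reduced because of a possible adverse event. Interventions and assessment procedures separately allows escalation to be adjusted or delayed for side effects. Suppose a participant is still on 315 mg BID on day 25. Under the BID line of the Design text, that participant is on schedule. Under Table 2, the participant is one step behind it. Whether this is planned dosing, a delay or an adjustment depends on which line is read. The week is also observed closely, with a weekly phone call during escalation and an on-site visit at week 4.

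**Working it through.** **Inputs.** Single doses, frequencies and day ranges come from Design, from Interventions and assessment procedures, and from Table 2, criterion 7. The target daily dose comes from Interventions and from Randomisation and blinding.

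**Step 1: reproduce the article's own figure.** Daily dose = single dose × doses per day. For the last step, 420 × 3 = 1,260 mg/d, which agrees with the stated target.

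**Step 2: convert every step.**

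| Step | Daily dose | Days, Design | Days, Interventions | Days, Table 2 |
|---|---|---|---|---|
| 60 mg TID | 180 mg | 1–7 | baseline–7 | 1–7 |
| 120 mg TID | 360 mg | 8–14 | 8–14 | 8–14 |
| 315 mg BID | 630 mg | **15–28** | **15–28** | **15–21** |
| 315 mg TID | 945 mg | 22–28 | 22–28 | 22–28 |
| 420 mg TID | 1,260 mg | 29–550 | not given | 29–550 |

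Only one entry differs between the versions: the end day of the 315 mg BID step.

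**Step 3: expand each full schedule over days 1–550.**

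- Design: no day is without a dose, and 7 days (22 to 28) carry two dose levels, 630 and 945 mg/d.
- Table 2: no day is without a dose, and no day carries two.
- Interventions: the same overlap on days 22–28 as in Design.

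**Step 4: size of the ambiguity.**

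- Per day: 945 − 630 = 315 mg. Relative to the lower figure, 315 / 630 = 50%.
- Over the week: 630 × 7 = 4,410 mg against 945 × 7 = 6,615 mg, a difference of 2,205 mg.
- Extent: 7 of the 28 days before the target dose (25%), and 7 of 550 treatment days (1.3%).

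Step 3 shows which printed schedule is free of overlap. It does not show which dose was intended or approved.

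**The case against.** The strongest reply is that this is one wrong date in a journal article and says nothing about the trial. Much of that stands.

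- **There are two versions, not three.** Design and Interventions agree with each other. Their near-identical wording fits one error that was copied, so the repetition is not evidence of two independent mistakes.
- **All three places list 315 mg TID for days 22–28.** The direct disagreement is only about when the preceding step ends, and a date slip is plausible.
- **The governing documents are not shown.** The article refers to an approved protocol and to staff trained in protocols and operating procedures. It says that the manufacturer receives the randomisation list, not that kits are made up from this text. A reader might infer that sites and the manufacturer cannot know the dose for that week. The article does not support that, because nothing in it says that anyone doses from the article.
- **The two lines are not meant to be added.** A reader might sum them to 630 + 945 = 1,575 mg/d, above the 1,260 mg/d target. The text describes successive escalations, and under that reading the dose would fall on day 29. The sum is not a reading that the article offers.
- **No harm to conduct is documented.** A reader might also infer that sites dosed differently, or that deviations were misrecorded. Nothing shows either. The tolerability outcome compares randomised arms, not sites, and the week-4 dose may vary by design because the investigator may delay escalation.

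What the reply does not remove is the contradiction itself. An article may leave detail to the full protocol, but this one states the schedule three times and disagrees with itself.

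**Conclusion.** The point holds as an internal contradiction in a stated dosing schedule. Design and Interventions give both 630 and 945 mg/d for days 22–28, Table 2 gives only 945 mg/d, and nothing ranks the versions. The planned dose is therefore not uniquely stated for 7 days of escalation, with a gap of 315 mg/d (2,205 mg over the week) between the readings.

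The consequence is confined to the reference dose for judging reductions, and any delayed escalation, in that week. The sample size, alpha, power and the 18-month MMSE analysis use none of these inputs.

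The conclusion rests on the printed text alone. Whether the approved protocol and site documents share the overlap cannot be told from the article. It is still worth settling promptly: the trial is running, the article reports 30 patients already started on medication, and the affected text concerns dosing in a trial whose first objective is safety and tolerability. No view is taken on which dose is right.

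**What to change.** Check the titration lines in Design, in Interventions and assessment procedures, and in Table 2, criterion 7, against the full approved protocol. Correct whichever of them departs from it, so that every titration day has exactly one stated dose. Confirm that the working documents at the sites carry that same single schedule. If they do, a published correction is enough. If they do not, the sponsor should establish which schedule was followed on days 22–28 before dose reductions in that week are counted.

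The cost is a text correction and a document check. No new data are needed, and the sample size and analysis do not change.
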